#### Adoption-preparation (baseline data collection) phase (6 months)

Staff at each site will be trained to enter data into SCCM’s research electronic data capture (REDCap) [60, 61]. These data will serve as a baseline for evaluating the change in bundle compliance at the end of the 30-month implementation phase associated with the implementation strategy.

##### Identify and train champions

Sites will choose a nurse and physician as site champions (i.e., clinicians supportive of implementation [39, 62]). Aggregate results from exploration phase surveys will be shared with site investigators at an in-person meeting hosted at SCCM.

##### Create a learning collaborative

Each site will develop a change team consisting of an ED physician, ED nurse, hospital quality improvement advisor, and data collector. A monthly virtual meeting will be conducted by the study team for each arm with the site teams, including review of educational approaches and materials.

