### Study setting

We will conduct this study at 18 diverse acute care hospitals in the USA. Hospital selection was based upon responses of ED leaders to a baseline survey to ensure a diverse and representative sample of hospitals. Considerations included hospital size, teaching status, and known improvement strategies. Discovery, the Society of Critical Care Medicine’s (SCCM) critical care research network, will serve as clinical and data coordinating center for the study. Sites were recruited from Discovery and via polling emergency medicine members of SCCM as to suitability of their hospital as a site. Both academic and community hospitals are included to support the pragmatic nature of the study and ensure generalizability. To account for baseline implementation efforts, prior to randomization, sites that reported less than 30% or more than 70% compliance with SEP-1 were not included for study participation. Patient inclusion criteria include suspected severe sepsis and/or septic shock in the ED with 2 out of 4 Systematic Inflammatory Response Syndrome (SIRS) criteria, evidence of organ dysfunction, and suspected infection—consistent with the criteria established for SEP-1 by CMS. Time zero (the beginning of measuring compliance with the 3-h bundle) is defined in the same manner as described by CMS—all three criteria have to be met within 6 h in order for the definition of time zero to be met. Patients will be excluded if, within 24 h of admission, they are made do-not-resuscitate/do-not-intubate, comfort measures only, or considered not eligible to full aggressive care because of patient or family wishes. For consistency, only hospitals utilizing Epic as their EHR were included. In addition, the decision was made by the investigators that if patients do not present with hypotension, but develop hypotension after the criteria for time zero are met, then no fluids will be given. This does not mean that no fluids will be given to a patient, but rather that, for the purposes of the AIMS study compliance with fluids will not be measured.

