### Randomization

Hospitals will be randomized to one of two arms (1- or 3-h bundle) in a 1:1 ratio. Randomization will be accomplished using randomly permuted blocks of variable size and controlling for academic or community status. Hospital physician and nurse dyads will be told which condition they were randomized to during in-person meetings at SCCM immediately prior to the Implementation Phase; separate meetings will take place for each study arm. Each arm will undergo a 30-month structured, collaborative implementation approach to operationalize compliance with their bundle assignment. The elements of both bundles are identical—only the timing is different (see Table 1). In this cluster-randomized clinical trial, the hospital is the unit of randomization. Hospitals will be informed as to their randomized arm after the baseline collection period. The randomization will be done by the study statistician and held only in the statistician’s computer until the reveal meeting at the end of the baseline period. Due to the pragmatic, open-label design of this trial and its objective measurement of study outcomes, the study staff, investigators, sites, and biostatisticians will not be masked to treatment condition once randomization occurs. Patients will receive standard of care for sepsis and their data will be collected retrospectively by the hospital each month.

**Table 1 Tab1:** 1- and 3-h bundle elements: quality and outcome indicator definitions and specifications

	**Definition of bundle element (quality indicator) or outcome measure obtained from the EHR by site staff**	**Both study arms**

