##### Audit, feedback and process evaluation of bundle implementation

Hospital sites in both arms will receive feedback on compliance every month [62, 63] including (1) review of successes and failures of implementation, (2) ongoing discussion of compliance barriers, and (3) methods for overcoming barriers. Learning collaborative meetings will be recorded for analysis in formative process evaluations.

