##### Compliance definition

This study will collect the date and time associated with each of these four measures: (1) when serum lactate level was collected, (2) when blood culture was collected, (3) when antibiotics were started, and (4) when fluids (30 ml/kg crystalloids) were started. Compliance is defined as to whether or not these date and time stamps were within 1 or 3 h (inclusive) of time zero depending on hospital randomization.

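### Aim 2 compliance is abstracted by unmasked site staff from a time zero resting partly on suspected infection; the objective-measurement rationale fits mortality, not compliance

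*Protocol article*

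**What the plan says.** All references are to the protocol article.

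- **Who collects.** Create a learning collaborative: "Each site will develop a change team consisting of an ED physician, ED nurse, hospital quality improvement advisor, and data collector". Under Randomization, the column heading of Table 1 describes each entry as a bundle element or "outcome measure obtained from the EHR by site staff". The same section says of patients that "their data will be collected retrospectively by the hospital each month".
- **Masking.** Randomization gives the open-label, pragmatic design and objective outcomes as the reason for no masking: "objective measurement of study outcomes, the study staff, investigators, sites, and biostatisticians will not be masked". Hospitals learn their arm only after baseline collection.
- **The clock.** Study setting follows the CMS definition, built on SIRS, organ dysfunction and suspected infection: "all three criteria have to be met within 6 h in order for the definition of time zero to be met". Table 1 instead counts from presentation in the ED.
- **The outcome.** Compliance definition: "This study will collect the date and time associated with each of these four measures" (lactate, blood culture, antibiotics, fluids). Each stamp is compared with time zero at 1 h or 3 h, by arm. Aim 2 scores compliance all-or-nothing and analyses it much as mortality is analysed.
- **Feedback.** Audit, feedback and process evaluation: "Hospital sites in both arms will receive feedback on compliance every month".
- **Alternative clock.** Subgroup analyses, under Aim 1, plans a sensitivity analysis with triage time as time zero.

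**The concern.** A death in hospital is the same event whoever records it. Compliance is an interval, and one end of it depends on when three criteria were met. One of these, suspected infection, has to be read from the chart. In the outcome period the readers are staff who know their hospital's deadline. The data collector among them belongs to the team charged with raising compliance, and the hospital sees its compliance figures monthly. The single sentence defending the lack of masking does not separate this outcome from mortality.

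If time zero were recorded later, compliance would rise with no change in care. The same few minutes are a larger share of a 60-minute window than of a 180-minute one, so even an equal shift in both arms need not cancel between them. Two readings are exposed: the Aim 2 hypothesis that compliance will be similar in the two arms, and the use of Aim 2 (Design considerations) to judge whether 3-h hospitals drifted towards the 1-h bundle.

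**Working it through.** **1. Anchors from the plan.** Recruitment and power expects 70% compliance in the 1-h arm; Table 4 has 70% and 80%. The plan uses these figures consistently:
- 0.80 × 18.9 + 0.20 × 26.1 = 20.3 and 0.70 × 16.2 + 0.30 × 24.4 = 18.7, as in Table 4.
- 105 × 1.5 = 157.5, rounded to 158; 158 / 0.70 = 225.7, against 230 stated.

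The plan gives no figure for a time-zero shift and no distribution of completion times. Everything below is therefore assumption.

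**2. Model.** Let F be the distribution of time from time zero to the last element. Recording time zero d later in every patient changes compliance at cutoff T by F(T + d) − F(T).

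- Exponential, t in hours: F1(t) = 1 − 0.30^t and F3(t) = 1 − 0.20^(t/3). At d = 0.25 h, F1(1.25) = 0.778 and F3(3.25) = 0.825.
- Log-normal, SD s of log time, d in minutes: Φ(z(0.70) + ln((60 + d)/60)/s) − 0.70 and Φ(z(0.80) + ln((180 + d)/180)/s) − 0.80.

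| Shape (same in both arms) | Shift | 1-h gain, points | 3-h gain, points | Ratio | Difference |
|---|---|---|---|---|---|
| Exponential | 5 min | 2.9 | 0.9 | 3.3 | 2.0 |
| Exponential | 10 min | 5.5 | 1.7 | 3.2 | 3.8 |
| Exponential | 15 min | 7.8 | 2.5 | 3.1 | 5.3 |
| Log-normal, s = 0.7 | 15 min | 10.0 | 3.0 | 3.3 | 7.0 |
| Log-normal, s = 1.0 | 15 min | 7.3 | 2.2 | 3.4 | 5.1 |
| Log-normal, s = 1.3 | 15 min | 5.7 | 1.7 | 3.4 | 4.0 |

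Across all equal-shape models tried (exponential, Weibull, log-normal, uniform) and shifts of 5 to 15 min, the ratio is 2.6 to 3.6. Some other shapes give larger gains at 15 min: 14.8 against 4.9 points for a Weibull with shape 2, and 17.5 against 6.7 for a uniform.

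**3. Where the factor breaks down.**
- Unequal log-normal spread, 5 min: SD 0.5 (1-h arm) and 1.0 (3-h arm) give 5.3 against 0.8, ratio 7.0. SD 1.5 and 0.4 give 1.8 against 1.9, ratio 1.0.
- One common distribution in both arms, which no longer matches 70% and 80%: log-normal SD 0.5 with 60% within 3 h gives 1.1 against 2.1 at 5 min, ratio 0.5. An exponential with 60% within 3 h gives 1.8, and one with a 1 h median gives 4.0.
- Partial shift: if one third of patients are shifted (assumption), the log-normal difference of 4.0 to 7.0 points becomes 1.3 to 2.3.

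**4. Difference-in-difference.** If the shift enters only the outcome period, the observed contrast is the true one plus (1-h gain − 3-h gain). This is zero only when the gains are equal. Nor does the odds scale cancel it. For the exponential at 15 min, the marginal odds go from 0.70/0.30 = 2.33 to 0.778/0.222 = 3.50 (ratio 1.50), and from 0.80/0.20 = 4.00 to 0.825/0.175 = 4.71 (ratio 1.18). The false interaction is 1.50 / 1.18 = 1.27.

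**5. Effect on levels.** In that case the expected gap of 80 − 70 = 10 points becomes 82.5 − 77.8 = 4.7, which favours a finding of similar compliance.

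**The case against.** The strongest points on the other side are these.

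- **Time zero has a fixed rule.** It follows CMS, and the article does not say who applies it. A reader might infer that each hospital sets its own time zero. Local assignment is plausible where site staff abstract the chart, but it is not stated. This stands.
- **The data form is not shown.** A reader might infer that the coordinating centre cannot recompute time zero because only four treatment stamps are listed. The list need not be exhaustive, the definition itself needs a recorded time zero, and the triage analysis needs a triage time. A condensed article would not list every field. This stands.
- **Compliance is already defined by time stamps.** The definition does not rest on the yes/no items of Table 1, and a triage clock is already planned. Both are true, but the triage analysis sits under Aim 1 and is not stated for compliance.
- **A shift in every patient is severe.** Fifteen minutes equals the whole reduction in median time to antibiotics assumed for the 1-h arm. Later charting of suspicion matters only where suspicion is the last criterion met. This stands and shrinks the effect.
- **The direction is not known.** Sites will also build automated sepsis alerts, which could move recorded recognition earlier. This stands.
- **The 10-point gap is not a benchmark for a difference-in-difference.** It is a post-intervention difference in levels, and no baseline compliance by arm is given. This stands.

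None of these makes compliance an objectively measured outcome in the sense in which mortality is one.

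**Conclusion.** The concern holds in a limited form. Unmasked site staff, with a data collector on the change team, abstract an outcome counted from a clock that depends partly on charted suspicion. The stated rationale does not cover that outcome. The bias is a possibility; nothing in the article shows that it occurs or that anyone would shade a record.

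For size, a 15 min shift in every patient gives about 6 to 10 points against 2 to 3 under log-normal spread of 0.7 to 1.3, with a ratio of 2.6 to 3.6 across the equal-shape models for 5 to 15 min. A reader might take a threefold effect as a property of this trial. It is a result of the equal-shape assumption and the 70% and 80% anchors; without them the ratio runs from about 0.5 to 7, so even the direction of the difference between arms can change.

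A reader might also extend the point to the primary outcome. The documents do not support that: whether a patient died in hospital does not depend on the clock.

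**What to change.** 1. Derive time zero and each element's compliance centrally from recorded time stamps, with one program fixed before the reveal and applied unchanged to the baseline and outcome periods. State in the protocol who assigns time zero.
2. If the data form lacks time stamps for the three time-zero criteria, add them.
3. Extend the triage-time sensitivity analysis to Aim 2 compliance, or repeat that analysis with the clock at the later of the SIRS and organ-dysfunction times. Neither depends on when suspicion was charted.
4. Reconcile the time-zero definition in Study setting with the presentation-based clock in Table 1.
5. Limit the objective-measurement sentence under Randomization to mortality.

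The cost is one derivation program, one further analysis, and at most three date-time fields per patient at sites that share one EHR. Trial status says baseline collection began on December 1, 2022, with randomization planned for the end of June 2023. If the criterion stamps were not captured, some baseline charts would have to be reopened. Patient care does not change.

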#### Implementation phase (30 months)

##### Conduct separate ongoing training virtual meetings for each arm

Following randomization, site teams will participate in virtual monthly learning collaborative meeting, focusing on content of the sepsis bundles, creating a team atmosphere and how to review and overcome barriers to implementation. Each learning session will include additional instruction on facilitating change, developing an information infrastructure to measure progress and quality improvement and implementation science theory. Sites in each arm will have access to a distinct on-line discussion forum to share ideas, questions, challenges, and solutions.

##### Develop and implement tools for quality monitoring (reporting tool)

Sites will (1) provide ongoing feedback and training of data collectors, (2) develop automated EHR alerts for identification of sepsis in the ED, (3) review order sets, and (4) assess physician and nurse engagement.

##### Audit, feedback and process evaluation of bundle implementation

Hospital sites in both arms will receive feedback on compliance every month [62, 63] including (1) review of successes and failures of implementation, (2) ongoing discussion of compliance barriers, and (3) methods for overcoming barriers. Learning collaborative meetings will be recorded for analysis in formative process evaluations.

#### Sustainment phase (12 months)

##### Outcome assessment and summative evaluation (6 months)

At the end of the 30-month implementation period, sites will continue to implement the 1 and 3-h bundles. Data collection and reporting will continue post-intervention to assess sustainability. Data collected during the 6-month outcome assessment phase will serve as the primary data set for analysis and for comparison to the 6-month period of baseline data. A mixed methods summative evaluation to measure change in barriers and facilitators identified in the exploration phase and bundle sustainment will be completed. We will administer the ILS [56], EBPAS-15 [57], ORIC, and ICS [58] measures, as well as the 40-item Program Sustainability Assessment Tool [64]. Semi-structured interviews will be repeated with key ED team members evaluating the EPIS framework and most effective implementation strategies.

##### Dissemination activities (6 months)

Following the data analysis, investigators will develop educational materials that summarize the findings of the trial as well as “how to guides” for generalizing the implementation strategy to other hospitals [65–68]. Investigators will disseminate results to national stakeholders (i.e., SCCM, Institute for Healthcare Improvement, professional societies, and hospital associations). Specifically, as indicated via letters of support, SCCM and the American College of Emergency Physicians (ACEP) will disseminate trial results through their communication channels, including discussion groups and social media accounts. In addition, trial findings will be published in peer-reviewed journals, presented at national and international conferences, and shared by study investigators via social media. Furthermore, de-identified data will be made available in a data repository in adherence with NIH’s Data Sharing policy.

### Recruitment and power

The study sample size will (4070 in each arm) provide adequate power to detect a difference-in-difference in hospital mortality between the pre-intervention period and the post-intervention period. This estimate is based upon the number of patients who receive care compliant with the respective bundles and associated hospital mortality. Analyzing ED patients included in the New York Sepsis Database, pre-intervention hospital mortality was 19.1% for those compliant with the 3-h bundle. Analyzing the data to create cohorts compliant with therapies at 1 h and at 3 h, the post-intervention hospital mortality of those receiving care compliant with the 1-h bundle was 16.2% and hospital mortality for those receiving care compliant with the 3-h bundle was 18.9% (preliminary data submitted to NHLBI R01 HL153268). This is based on the assumption that in the post-intervention period, the median time to antibiotics will be reduced by a quarter of an hour (25% reduction) in the 1-h arm. This quarter of an hour reduction in time to antibiotics translates to a 0.2% reduction in hospital mortality. Table 3 summarizes the assumptions used in the power calculation.

**Table 3 Tab3:** Assumptions for Donner and Klar’s cluster-randomized power calculation using a mixed model test for two proportions in a 2-level hierarchical design. An intraclass correlation coefficient of 0.025 is based on ED patients in the New York Sepsis Clinical Database

Compliant ED patients with the bundle	Pre-intervention mortality, %	Intervention period	Post-intervention mortality, %	Difference	Difference in difference
3-h arm	19.1		18.9	0.2%	2.7%
1-h arm	19.1		16.2	2.9%	

Using the power estimate methods of Donner and Klar, nine hospitals per arm with a minimum of 105 patients in each hospital will give 80% power to detect a 2.7% difference-in-difference in mortality, with *α* = 0.05, ICC = 0.025, and an equal number of hospitals per arm. To account for limitations in preliminary data, we increased the target number of patients by 50% to 158 patients. Since we expect bundle compliance in the 1-h arm to be 70%, 230 *total subjects* per hospital are needed. Table 4 shows the expected overall hospital mortality in the intent-to-treat analysis based on these assumptions. Multiple imputation will be used to handle missing data.

**Table 4 Tab4:** Estimated pre- and post-intervention overall mortality used in the intent-to-treat analysis

ED patients	Pre-intervention^1^	Compliant group		Non-compliant group		Post-intervention overall mortality, %
		Adherent, %	Mortality, %	Non-adherent, %	Mortality, %	
3-h arm	23.2	80	18.9	20	26.1	20.3
1-h arm	23.2	70	16.2	30	24.4	18.7

^1^Based on analysis of the New York Sepsis Database

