### Analysis plan

#### Aim 1: 1-h bundle will have significantly lower patient mortality and improve all secondary outcomes

##### Primary outcome analysis

An intention to treat analysis of patient mortality in each arm will be evaluated in 2 ways: (1) the difference, in primary outcomes (hospital mortality), between the two arms during the 6-month baseline assessment and the 6-month outcomes assessment, and (2) the comparison between the first two differences (i.e., difference-in-difference estimation). This difference-in-difference analysis will be the *primary analysis* to assess the *primary hypothesis* of Aim 1: the 1-h bundle will result in lower mortality than the 3-h bundle. Both absolute and risk-adjusted hospital mortality will be reported. Random-effects logistic regression will evaluate all the mortality differences. The random term will be the hospital. This model will contain three binary risk factors: (1) 1-h arm vs. 3-h arm, (2) 6-month baseline period prior to randomization vs. 6-month outcome assessment phase, and (3) the interaction of these two terms. The effect of the intervention and the effect of the two time periods will be quantified by odds ratios while the differences in hospital mortality will be quantified by model probabilities. Additionally, the model will be adjusted for hospital level 3-h bundle compliance prior to intervention along with patient and hospital characteristics.

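### The stated 80% power is for a 2.7-point effect in bundle-compliant patients, but the primary test is intention-to-treat, where Table 4 implies 1.6–1.7 points and no power is given

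*Protocol article*

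**What the plan says.** Under Recruitment and power, the protocol article describes the target population of the calculation: "This estimate is based upon the number of patients who receive care compliant with the respective bundles and associated hospital mortality". Table 3 gives compliant-patient mortality of 19.1% before and 18.9% after in the 3-h arm, and 19.1% before and 16.2% after in the 1-h arm. The changes are 0.2 and 2.9 points, so the difference-in-difference is 2.7 points. The power claim, which concerns hospital mortality, is that "nine hospitals per arm with a minimum of 105 patients in each hospital will give 80% power to detect a 2.7% difference-in-difference". The significance level there is 0.05 and the intraclass correlation 0.025.

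The 105 is raised by 50% to 158 for limitations in the preliminary data. It is then raised to 230 in total per hospital: "Since we expect bundle compliance in the 1-h arm to be 70" per cent. The total is given as 4070 in each arm.

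The section then says: "Table 4 shows the expected overall hospital mortality in the intent-to-treat analysis based on these assumptions". Table 4 lists 23.2% before in both arms, and 20.3% (3-h) and 18.7% (1-h) after. No power is attached to these figures.

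Under Primary outcome analysis: "An intention to treat analysis of patient mortality in each arm will be evaluated in 2 ways". The difference-in-difference is named there as the primary analysis, fitted by random-effects logistic regression with hospital as the random term.

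**The concern.** Power is stated for one contrast and the primary hypothesis is tested on another. In an intention-to-treat analysis the non-compliant patients stay in both arms, and Table 4 shows that they shrink the expected contrast from 2.7 to under 1.7 points. Dividing 158 by 0.70 makes the expected number of compliant patients equal the target. That would suit an analysis restricted to compliant patients, but it does not restore the precision needed for a smaller effect in everyone.

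This matters for how a null result is read. Under Anticipated findings and impact, the article says that if the bundles do not differ, efforts should return to compliance with the 3-h bundle, and it calls a negative finding particularly important. That inference needs known and adequate power for the intention-to-treat contrast.

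**Working it through.** **Inputs.** All are from the protocol article (Recruitment and power, Tables 3 and 4): 9 hospitals per arm, 105 / 158 / 230 patients per hospital, ICC 0.025, α 0.05, and the mortality figures above. Sidedness is not stated; I assume two-sided.

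**1. The plan's chain of numbers.**
- 105 × 1.5 = 157.5, stated as 158.
- 158 / 0.70 = 225.7, stated as 230.
- 225.7 × 9 hospitals × 2 periods = 4063, stated as 4070.

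So 4070 per arm appears to cover both periods together, with 230 per hospital per period. This reading is inferred, not stated.

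**2. The intention-to-treat contrast from Table 4.**
- 3-h arm: 0.80 × 18.9 + 0.20 × 26.1 = 20.34%.
- 1-h arm: 0.70 × 16.2 + 0.30 × 24.4 = 18.66%.
- Both arms start at 23.2%, so the difference-in-difference is 20.34 − 18.66 = 1.68 points (1.6 from the rounded cells).

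**3. Inflation needed against inflation applied.**
- Effect ratio alone: (2.7 / 1.68)² = 2.58.
- Intention-to-treat mortality is also higher, so its variance is larger. The sum of p(1 − p) over the four cells is 0.670, against 0.598 for compliant patients. 2.58 × 0.670 / 0.598 = 2.89.
- Needed for dilution alone: about 2.6–2.9.
- Applied, counting both steps: 230 / 105 = 2.19. Of this, 1/0.70 = 1.43 is the compliance step and 1.5 is the allowance for preliminary data.

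**4. Problem (a): accept the stated 80% at 105 per hospital.**
- Implied standard error: 2.7 / (1.960 + 0.842) = 0.964 points.
- Power for 1.6–1.7 points at that precision: 38–42%.
- At 230 with no clustering limit: SE = 0.964 × √(105/230) = 0.651. Power is 69–74%, or 64–69% with the larger intention-to-treat variance.
- At 230 with the design effect 1 + (m − 1) × 0.025: this is 3.6 at 105 and 6.725 at 230, so effective patients per hospital rise only from 29.2 to 34.2. SE = 0.964 × √(29.2/34.2) = 0.890. Power is 44–48%, or 40–44% with the larger variance.

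**5. Problem (b): calculate directly from the plan's inputs.** With stable hospital effects, the hospital term cancels in the difference-in-difference, and SE = √[(1 − 0.025) × Σp(1 − p) / (9m)], where m is patients per hospital per period.

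| Contrast | m per hospital per period | SE (points) | Power |
|---|---|---|---|
| 2.7 points, compliant | 105 | 2.48 | 19% |
| 2.7 points, compliant | 230 | 1.68 | 36% |
| 1.68 points, intention-to-treat | 230 | 1.78 | 16% |
| 1.68 points, intention-to-treat | 452 (4070 per arm per period) | 1.27 | 26% |

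The first row is the plan's own case, stated as 80%, and it does not reproduce. A post-period comparison of 18.9% with 16.2% at 105 per hospital and a design effect of 3.6 gives about 13%. Even with no clustering that comparison gives about 34%. One-sided testing raises these figures (29% for the first row) but does not bring them near 80%.

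The intention-to-treat difference detectable with 80% power at 230 per hospital per period is (1.960 + 0.842) × 1.78 = 5.0 points on the same assumptions.

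**6. Text against Table 3.** The text ties the 1-h arm's gain in antibiotic time to a small benefit: "This quarter of an hour reduction in time to antibiotics translates to a 0.2% reduction in hospital mortality". Table 3 gives 0.2% to the 3-h arm and 2.9% to the 1-h arm. The two do not agree.

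**7. Source of the 2.7.** The text defines the starting value thus: "pre-intervention hospital mortality was 19.1% for those compliant with the 3-h bundle". The 1-h row of Table 3 starts from that 19.1% and ends at 16.2% in 1-h-compliant patients. Part of the 2.9-point fall may therefore be a change in which patients are counted.

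**The case against.** The article is open about its basis. It says that the estimate concerns compliant patients and it directs the reader to Table 4 for intention-to-treat mortality. It also adds 50% beyond the compliance step, so it would be wrong to infer that 1.43 is the only inflation. Observational planning inputs are normal and are disclosed. All of this stands, but disclosure does not supply the missing power, and the total of 2.19 is still short of 2.6–2.9.

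A reader might attribute the whole drop from 80% to 16% to the intention-to-treat mismatch. The documents do not support that. In the direct calculation, power for 2.7 points at 230 per hospital is already only 36%. The fall from 80% to 36% reflects a figure that does not reproduce; dilution accounts for the fall from 36% to 16%.

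Two other inferences are tempting and should not be drawn:
- **Scaling 0.2% per quarter-hour** to ask how many hours would yield 2.7 points. This assumes a linear effect, and that a shift in median antibiotic time equals the gap between the bundle windows. The article states neither, and the bundle has other elements.
- **Counting compliant baseline patients** from the 30–70% SEP-1 site limits. That is a site-selection rule, and an intention-to-treat analysis requires no number of compliant patients.

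Finally, 1.68 is no firmer than 2.7, because Table 4 is built from the same 16.2% and 18.9%.

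**Conclusion.** The point holds. The stated power does not belong to the primary test, and no calculation tried gives 80% for the Table 4 contrast. Two problems should be kept apart:

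- **Wrong contrast.** Even if the 80% is accepted, intention-to-treat power at 230 per hospital is about 64–74% without a clustering limit and about 40–48% with the ICC 0.025 design effect.
- **Figure that does not reproduce.** The direct calculation gives 19–36% for the 2.7-point effect and about 16% for the intention-to-treat effect (26% if 4070 is per arm per period).

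These results assume two-sided α 0.05, 230 per hospital per period and, for the direct calculation, hospital effects that are stable between periods. Unstable effects would lower the direct figures. The spread between the two sets depends on the method and on whether the 80% is believed, so no single value should be quoted as the power of the trial.

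**What to change.** In Recruitment and power:

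1. State the power and the detectable difference for the Table 4 intention-to-treat contrast, with 9 hospitals per arm and the planned numbers. Say whether 230 and 4070 are per period and whether the test is one- or two-sided.
2. Recompute the 80% for 2.7 points at 105 per hospital, showing formula and inputs, or correct it.
3. Keep 158 / 0.70 as the derivation of 230, but do not present it as a power adjustment.
4. State that both 2.7 and 1.68 rest on observational mortality in compliant cohorts, and that the 1-h row of Table 3 moves from 3-h-compliant to 1-h-compliant patients.
5. Reconcile the quarter-hour/0.2% sentence with Table 3.

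The cost is a rewritten section and revised text around Tables 3 and 4. The stated power will look less favourable, and the conclusions planned for a null result would need to reflect that. Whether the design should change in response is a separate decision for the sponsor.
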